### Sample size

A conservative sample size estimate is 6840 total patients (120 patients per clinic from 57 clinics) that assume a minimum of 30 eligible patients per clinic per year based on the smallest clinic. We present the power calculations assuming an intraclass correlation coefficient (ICC) between 0.02 and 0.05. With this design, we will have 80% power (alpha=0.05, two-sided) to detect a standardized effect size of 0.118 (ICC=0.02) to 0.121 (ICC=0.05). For our primary effectiveness outcomes, we estimate a standard deviation (SD) of 10.1 percentage points for percentage change in weight using our pilot study, and a similar SD estimate of 10.7 for absolute (kg) change in weight. Thus, with 80% power we can detect a mean difference in weight change of 1.19 (ICC=0.02) to 1.22 (ICC=0.05) percentage points between the control and intervention conditions, and a mean difference in absolute weight change of 1.26 kg (ICC=0.02) to 1.29 kg (ICC=0.05).

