#### Clinician workflow

To optimize efficiency and guide care, health care providers are encouraged to use the PATHWEIGH weight management SmartSet in Epic. A SmartSet is a documentation template used in the ambulatory setting comprised of a group of orders and other elements, such as notes, chief complaints, medications, and levels of service charges, that are commonly used together to document a specific type of visit. This SmartSet addresses the following.
Diagnosing overweight or obese patients with a BMI > 25 kg/m^2^ or > 30 kg/m^2^, respectively, recognizing these as bona fide disease states [6]Linking diagnoses for weight-related comorbidities to facilitate reimbursementPre-populating information from the patient weight management questionnaire to serve as documentation and to guide the clinician-patient discussion, and flagging weight management strategies based on guidelines from the Obesity Society [32], specifically, the discussion of lifestyle change for patients with BMI ≥ 25 kg/m^2^, consideration of medications impacting obesity as well as anti-obesity medication at BMI ≥ 30 kg/m^2^ (or BMI ≥ 27 kg/m^2^ with weight-related comorbidities) and consideration of bariatric surgery for BMI ≥ 40 kg/m^2^ (or BMI ≥35 kg/m^2^ with weight-related comorbidities)Providing options for orders that include laboratory testing, referrals, or procedures

Behavioral health professionals work alongside many of the primary care providers and are encouraged adjuncts to facilitate weight loss. Use of the PATHWEIGH tools is entirely optional for clinicians. Use may be deployed by the clinicians in advance of the visit or if they or the patient spontaneously decides to prioritize weight management. The process strongly encourages regular follow-up (usually at 4–6 week intervals and more often initially). A key advantage is that the clinician is the patient’s regular provider and will have an ongoing relationship with the patient over time and can safely manage or discontinue medications or other issues for weight-related comorbidities.

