#### Analysis

A generalized linear mixed modeling strategy will be employed to account for multiple levels of correlation (i.e., between patients within practices and between measurements on a single patient over time) [44]. This approach allows for the most efficient use of data if any follow-up measurements are missing for some subjects. We will follow an intention-to-treat approach for our primary analysis, i.e., patients will be analyzed according to their clinic’s intervention condition (PATHWEIGH vs. SOC) at the time of the patient’s index visit. An index visit will be defined as the patient’s first weight-prioritized visit in an intervention condition. Follow-up visits at which weight is recorded will be associated with the intervention status of the patient’s preceding index visit.

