For the primary analysis, although the parameter of interest is weight change at 6 months, weight collected from baseline to approximately 9 months post-baseline for the individual patient will be included in the primary analysis because patients may not have visits with recorded weight within the 6-month time frame. The mixed model will include random intercepts for patient, provider, and clinic, along with fixed effects for time and intervention condition. The time effects are two-fold: (i) calendar time, divided into four 1-year periods and included as a categorical variable to flexibly model its effect on the outcome and account for temporal trends, and (ii) individual patient time, included as a continuous variable (i.e., time from baseline) to accommodate varying visit times determined by each patient’s visit schedule. The intervention condition variable will be a binary indicator that is equal to zero if the patient’s index visit occurs at a clinic when it is in the control condition and becomes equal to 1 when the patient has an index visit at a clinic after it has crossed into the intervention condition. Patient-, provider-, and practice-level covariates will be included in models if deemed to be potential confounders in univariate models. An additional fixed effect for the interaction between patient time and intervention condition will be used to estimate the parameters of primary interest, i.e., the difference in change in outcomes over time between the intervention and control conditions. The primary analysis will test the null hypothesis that the interaction effect coefficient is equal to zero to determine whether there is a significant difference in weight change between the PATHWEIGH and SOC conditions. Using the model, we will report the mean weight change in the control and intervention groups and their difference at 6 months, with corresponding 95% confidence intervals and *p* values.

To examine the secondary binary outcomes of weight maintenance (defined as < 10% weight gain at 12 and 18 months), we will use generalized linear mixed models. Since this analysis will involve a single outcome per patient, the model will only include a random intercept for provider and clinic. The test of intervention effectiveness will be captured by the fixed effect term for the intervention condition.

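### The primary test is a slope difference, but the primary model has random intercepts only, so its p value and confidence interval omit the clustering of weight change that the sample size assumes

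*Protocol article*

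**What the plan says.** The Aim 1 Analysis section sets out the purpose of the model: "A generalized linear mixed modeling strategy will be employed to account for multiple levels of correlation", naming patients within practices and repeated measurements on a patient. It then fixes the random part: "The mixed model will include random intercepts for patient, provider, and clinic, along with fixed effects for time and intervention condition". Patient time enters as a continuous variable. On the test it says: "The primary analysis will test the null hypothesis that the interaction effect coefficient is equal to zero". The 6-month difference, its 95% CI and its p value are to come from this model. On the data used: "weight collected from baseline to approximately 9 months post-baseline for the individual patient will be included in the primary analysis".

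The Sample size section says: "We present the power calculations assuming an intraclass correlation coefficient (ICC) between 0.02 and 0.05". It converts the resulting standardised effects to kilograms with a pilot SD of 10.7 kg for change in weight (0.118 × 10.7 = 1.26; 0.121 × 10.7 = 1.29). The ICC is thus applied to weight change.

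**The concern.** A random intercept moves all weights of a patient, provider or clinic up or down together. It describes who is heavier, not who loses more. Because the test concerns change, the intercepts drop out of it. The model then treats all patients and clinics in a condition as sharing one slope, with everything else left to the residual.

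The protocol does not believe that. Its power calculation lets change cluster by clinic, and its second hypothesis expects patient, clinician and clinic characteristics to mediate and moderate weight loss. If change does vary by clinic or patient, the model's standard error is too small and a trial with no effect is declared positive more often than 5% of the time. The test affected is the one primary test of the trial.

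**Working it through.** **Inputs from the protocol.** Clinics per sequence 20/18/19 (Table 1); three steps, four one-year periods, all clinics starting in control (Design and randomization); 30 patients per clinic-year, 6840 in total, ICC 0.02 to 0.05, two-sided alpha 0.05, 80% power, SD of change 10.7 kg (Sample size).

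**Assumptions, not in the protocol.** Weights per patient, visit-level SD, and any clinic size other than 30 per year.

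**1. The plan's own figure.** Hussey–Hughes variance with total variance 1, τ² = ICC, σ² = (1 − ICC)/30, C = 57, T = 4:

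Var = Cσ²(σ² + Tτ²) / [(CU − W)σ² + (U² + CTU − TW − CV)τ²]

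- U = 20×3 + 18×2 + 19×1 = 115
- W = 20² + 38² + 57² = 5093
- V = 20×9 + 18×4 + 19×1 = 271
- CU − W = 1462; U² + CTU − TW − CV = 3626
- ICC 0.02: Var = 0.2098/120.28 = 0.001744, SE 0.0418, detectable effect 2.80 × SE = 0.117
- ICC 0.05: Var = 0.4182/227.60 = 0.001837, SE 0.0429, detectable effect 0.120

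The protocol gives 0.118 and 0.121, so its figures are reproduced by a model that does carry clinic variance in change.

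**2. What the analysis model carries.** Weight at time t = clinic, provider and patient intercepts + period effect + condition effect + (β + δX)t + residual. Subtracting two weights of one patient leaves (β + δX)(t₂ − t₁) plus a difference of residuals. No clinic, provider or patient term remains.

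**3. Clinic level alone.** Calendar period enters only as a main effect, so it too cancels from change. The contrast is in effect pooled intervention minus pooled control change. Intervention clinic-periods: 115. Control: 20×1 + 18×2 + 19×3 = 113.

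- Clinic weights in the contrast: 3/115 − 1/113 = 0.01724; 2/115 − 2/113 = −0.00031; 1/115 − 3/113 = −0.01785
- Sum of squares: 20×0.01724² + 18×0.00031² + 19×0.01785² = 0.0120
- Model variance, patients independent: 1/(115×30) + 1/(113×30) = 0.000585
- True variance: ICC × 0.0120 + (1 − ICC) × 0.000585

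| ICC | True variance | Ratio to model | SE ratio | 1.96 / SE ratio | Type I error |
|---|---|---|---|---|---|
| 0.02 | 0.000240 + 0.000573 = 0.000813 | 1.39 | 1.18 | 1.66 | 9.6% |
| 0.05 | 0.000600 + 0.000556 = 0.001156 | 1.98 | 1.41 | 1.39 | 16.3% |

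Thirty per year is the stated minimum, based on the smallest clinic. At an assumed 100 per clinic-year the same formula gives 20% and 35%.

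**4. Patient level alone.** For m equally spaced weights, with visit SD s, slope SD b and S the sum of squared deviations of the visit times:

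true/model variance = (s²/S + b²) / (s²/S + b²/(m − 1))

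With m = 2 the ratio is exactly 1, because the residual absorbs slope variation. Example with s = 2 kg: the SD of true 6-month change is √(10.7² − 2×2²) = 10.32 kg, so b = 1.72 kg/month. Three weights three months apart give S = 18, a ratio of (0.222 + 2.958)/(0.222 + 1.479) = 1.87, an SE ratio of 1.37 and a type I error of 15%. For s from 1 to 5 kg, three weights give 10 to 16% and seven weights 27 to 42%.

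**5. Both levels, simulated null trials** (200 per setting in the main set, Monte Carlo error about 2 to 4 points):

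| Setting | ICC 0.02 | ICC 0.05 |
|---|---|---|
| Two weights, 0 and 6 months | 11–12% | 18–21% |
| About 3 weights, visit SD 2 kg | 35% | 40% |
| About 3 weights, visit SD 5 kg | 27% | not run |
| Baseline plus 3, visit SD 5 kg | 24–27% | 32–35% |
| Same, 150 per clinic-year | 42–48% | 59–66% |

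**6. With slopes added.** With visit SD 2 kg and about 3 or 6 weights per patient, the intercept-only model SE was 0.12 to 0.18 kg against an empirical SD of 0.31 to 0.38 kg, and rejection was 35 to 62%. Adding patient and clinic random slopes, at known variance components, gave a model SE of 0.27 to 0.28 kg, an empirical SD of 0.25 to 0.31 kg and rejection of 3 to 9% (150 trials per setting), consistent with 5%.

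**The case against.** The best defence is that the size depends on quantities the protocol does not give. The window runs to about 9 months because some patients will lack a weight within 6 months, so data may be sparse. With exactly two weights per patient the patient-level part vanishes. It also vanishes if all of the 10.7 kg SD is visit noise: simulated rejection was then 6% without clinic variation. That second case is implausible for weight change, but the first is a fair limit. Neither removes the clinic-level part.

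The article also does not state the residual covariance or the variance estimator. A reader might infer that errors are assumed independent; the text does not say so. An unseen analysis plan could add serial correlation, which might reduce the patient-level part but not the clinic-level part, or clinic-robust standard errors, which would be one of the remedies below. The random effects themselves, however, are stated and not left open.

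Three further inferences are not supported:

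- **That the error is several times 5% whatever the data.** The larger figures need assumed visit noise, more weights per patient or larger clinics. Growth with clinic size comes only from clinic clustering: at 150 per clinic-year and ICC 0, simulated rejection was 13 to 16%.
- **That the SE of about 0.45 kg implied by the power section (1.26/2.80) measures the shortfall.** That calculation adjusts change for calendar period, while the analysis model enters period only as a main effect. The gap therefore mixes in a separate issue.
- **That provider-level variation has a known effect.** The model omits it too, but it was not simulated.

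**Conclusion.** Wrong as written. The direction is firm: under the protocol's own ICC for change, a model with random intercepts only gives an anti-conservative primary test. On the protocol's inputs alone, the type I error is about 10% (ICC 0.02) to 16% (ICC 0.05), and about 11 to 21% in simulations with two weights per patient.

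Anything beyond that is conditional: about 25 to 40% with 3 to 4 weights per patient and a visit-level SD of 2 to 5 kg, and, at an assumed 150 patients per clinic-year, about 42 to 48% at ICC 0.02 and 59 to 66% at ICC 0.05. Even the mildest of these cases at the protocol's ICC is enough to require a correction before the primary analysis.

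**What to change.** Add random slopes on patient time at patient and clinic level, and at provider level if estimable, and take the primary p value and 95% CI from that model. Alternatively, keep the stated random effects and use clinic-level cluster-robust standard errors with a small-sample correction. The plan should name in advance which of the two is primary. A clinic-by-period random slope is optional; patient and clinic slopes were enough to bring rejection near 5% in the settings checked, though the robust alternative was not simulated.

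The change needs no new data, only revised wording and some computing time. Its cost to the trial is a wider reported interval.

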### Design and randomization

We will use a type 1 hybrid effectiveness-implementation stepped wedge cluster randomized design to assess both patient-level clinical and practice-level implementation outcomes [25, 26]. The intervention will be implemented sequentially in the 57 participating clinics in three steps over a 4-year period (Fig. 2). All sites will start in the control condition of SOC for weight management. Every year, one sequence of clinics will transition to the intervention condition after which the use of PATHWEIGH will be encouraged for all weight-prioritized visits and corresponding PATHWEIGH implementation strategies will be provided. Clinics were randomly assigned by the study statistician to each sequence using covariate constrained randomization [30] to achieve balance on clinic type (academic, affiliate, non-academic), clinic location (urban/suburban vs. rural), provider type (family medicine (FM), general internal medicine (GIM), or both), annual number of patient visits, and patient insurance status (percentage Medicaid) (Table 1). A stepped wedge extension for this procedure was used to account for the proportion of the study period that each of the sites spend in the control and intervention periods [30]. For additional details about the randomization procedure see Additional file.

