**Fig. 2 Fig2:**
[figure not shown]
Study diagram for the PATHWEIGH study, a stepped-wedge cluster hybrid type 1 randomized controlled trial design

**Table 1 Tab1:** Characteristics of participating practices and patients by randomization sequence

Site characteristic	Sequence 1 (20 clinics)	Sequence 2 (18 clinics)	Sequence 3 (19 clinics)
**Type,** *n*			
Academic	1	1	2
Affiliate	4	2	2
Non-academic	15	15	15
**Location,** *n*			
Urban	17	16	16
Rural	3	2	3
**Specialty,** *n*			
Family Medicine only (FM)	10	9	11
General Internal Medicine only (GIM)	6	6	4
Mixed FM/GIM	4	3	4
**Number of patients visits in 2019,** median (IQR)	10,589 (6059–22,233)	13,579 (7666–20,035)	9815 (3552–29,910)
**Percentage Medicaid,** median (IQR)	3.5 (2.0–5.0)	5.0 (3.0–7.0)	2.5 (1.8–7.0)

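### With random intercepts only, the primary time-by-condition test can be biased if follow-up visits track weight loss more closely under PATHWEIGH than under standard of care

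*Protocol article*

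**What the plan says.** The Protocol article, Aim 1, Analysis, fixes the primary model: "The mixed model will include random intercepts for patient, provider, and clinic, along with fixed effects for time and intervention condition". Patient time is continuous, and visit times follow each patient's own schedule. Weights from baseline to about 9 months are used, and the hypothesis test is on the interaction of patient time with condition. No random slope for patient time is mentioned.

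On incomplete follow-up, the same section says: "This approach allows for the most efficient use of data if any follow-up measurements are missing for some subjects". It expects the primary estimate to be conservative. It adds two secondary analyses, one restricting PATHWEIGH patients to those who received it and one widening the cohort to all patients eligible by age and BMI.

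On visits, Clinician workflow says of PATHWEIGH: "The process strongly encourages regular follow-up (usually at 4–6 week intervals and more often initially". The SOC section states no follow-up interval. Table 3 shows that weights come from the electronic record during routine care, so there is no scheduled 6-month weighing.

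**The concern.** When patients' true slopes differ, a random-intercept model does not average them equally. A patient weighed often over a long span pulls the slope more than a patient weighed twice. That is harmless while the visit pattern is unrelated to the trajectory. It is not harmless if patients who are losing weight return more often, and this link is stronger in one condition than in the other.

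PATHWEIGH sets out to change the visit pattern, so a difference between conditions is plausible. The tested coefficient would then differ from the difference in mean 6-month change per patient, even if every patient's path were a straight line. This is an error in the estimate, not only in its standard error. The receipt-based secondary analysis reuses the same models. The all-eligible analysis addresses who enters the cohort, not how often they are weighed afterwards.

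**Working it through.** **1. The plan's own yardstick.** Inputs from Sample size, Design and randomization, and Table 1: "80% power (alpha=0.05, two-sided"; 57 clinics; 30 patients per clinic-year; 4 one-year periods; sequences of 20, 18 and 19 clinics; ICC 0.02 to 0.05. The Hussey-Hughes variance is

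Var = Iσ²(σ² + Tτ²) / [(IU − W)σ² + (U² + ITU − TW − IV)τ²],

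with I = 57, T = 4, total variance 1, τ² = ICC and σ² = (1 − ICC)/30.
- U = 20×3 + 18×2 + 19×1 = 115
- W = 20² + 38² + 57² = 5093
- V = 20×9 + 18×4 + 19×1 = 271
- IU − W = 1462, and the bracket multiplying τ² is 3626

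ICC 0.02: Var = 0.2098/120.28, SE 0.0418, times 2.80 = 0.117. ICC 0.05: Var = 0.4182/227.60, SE 0.0429, times 2.80 = 0.120. A t reference with 167 df gives 0.118 and 0.121, the plan's figures. Times 10.7 kg, these are 1.26 and 1.29 kg. The yardstick is sound.

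**2. The weighting.** With between-patient variance large relative to residual variance, a patient's weight in the common slope is close to w = Σ(t − t̄)², with t in months.
- Weighed at 0 and 6: w = 9 + 9 = 18.
- Weighed every 1.5 months from 0 to 9: w = 2×(20.25 + 9 + 2.25) = 63, which is 3.5 times as much.

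**3. Size with evenly spaced visits over 9 months.** Assume normal slopes with SD s (kg per 6 months), no true effect, and dependence under PATHWEIGH only. The half losing more has weight w_L and the other half w_O. The losing half's mean slope is √(2/π) = 0.798 SD below average, so

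false difference = −0.798 s (w_L − w_O)/(w_L + w_O).

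The weights are 40.5, 45, 50.6 and 63 for 2, 3, 4 and 6 follow-ups. Each cell gives formula / simulation in kg. The simulation uses baseline SD 20 kg and residual SD 2 kg, with Monte Carlo error about 0.1 kg.

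| Follow-ups, losing v other half | s = 10.3 | s = 5 | s = 3 |
|---|---|---|---|
| 4 v 3 | −0.48 / −0.43 | −0.23 / −0.23 | −0.14 / −0.16 |
| 4 v 2 | −0.91 / −0.93 | −0.44 / −0.44 | −0.27 / −0.24 |
| 6 v 3 | −1.37 / −1.42 | −0.66 / −0.69 | −0.40 / −0.41 |
| 6 v 2 | −1.79 / −1.79 | −0.87 / −0.86 | −0.52 / −0.52 |

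The value s = 10.3 makes the SD of 6-month change √(10.3² + 2×2²) = 10.7 kg, the plan's figure. It therefore reads that SD as almost wholly slope heterogeneity, which the plan does not say. The smaller values cover the alternative.

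**4. Size with irregular visits (about 3 on average).** Here the visit rate is multiplied by a factor for each SD of weight loss, under PATHWEIGH only.
- s = 10.3: factor 1.1 gives −0.8 kg; 1.25 gives −1.8 kg; 1.5 gives −3.3 kg.
- s = 5: 1.25 gives −0.9 kg; 1.5 gives −1.6 kg.
- s = 3: 1.25 gives −0.5 kg; 1.5 gives −1.0 kg.

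If visits respond to loss already observed (2.6 v 2.2 visits), the result is −1.1 kg at s = 10.3, −0.3 kg at s = 5 and −0.1 kg at s = 3.

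**5. Conditions under which it vanishes.**
- Twice as many visits under PATHWEIGH (6 v 3), unrelated to loss: 0 within simulation error.
- Same dependence in both conditions (SD of change 8 kg, about 2.6 v 4.0 visits): −0.05 kg (SE 0.05); with weaker dependence, −0.16 kg (SE 0.11).
- SOC dependence about half as strong, same set-up: −0.82 kg.

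**6. Effect of the remedies.** At s = 10.3, adding a random patient slope brings the false effect to 0.0–0.1 kg when visits are evenly spaced or depend on observed weights. When visits depend on the unobserved slope, it falls from 1.8 to 0.6 kg and from 3.3 to 1.1 kg. With smaller slope SD it helps less in that last case: at s = 5 and factor 1.25, a repeat run gave 0.9 falling to about 0.5 kg. One weight nearest month 6 (SD of change 8 kg) cut 0.7 to 0.2 kg and 1.3 to 0.4 kg.

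**The case against.** A reader might infer that more frequent visits under PATHWEIGH by themselves create a false effect as large as the detectable difference. The documents do not support that. Frequency unrelated to trajectory produces no bias, and dependence of equal strength in both conditions largely cancels. Nothing shows that SOC attendance is unrelated to weight loss: SOC is described as highly variable, and no interval is given for it. Patients doing well under SOC may return more often too.

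The contrast in visit frequency may also be modest. Clinicians may decline to use the tools, each clinic or provider sets how many weight-prioritized visits to offer, non-users stay in the intention-to-treat comparison, and any visit with a recorded weight counts. Finally, sensitivity analyses for informative visits are often left to an analysis plan, which is not shown here.

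All of this limits the size and the certainty. It does not remove the point, because the article itself fixes a primary model with intercepts only, and that choice makes the test depend on who is weighed most. The random-effects structure of the primary model is stated, not deferred.

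**Conclusion.** The concern holds in conditional form. The tested interaction is biased if visit frequency depends on weight trajectory to a different degree in the two conditions. It favours PATHWEIGH if successful patients attend more there, and goes the other way if they stop attending, so the plan's expectation of a conservative estimate cannot be relied on for this source of error.

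The size rests on three quantities the documents do not give: the between-patient slope SD, the visit pattern by condition, and the strength of its link to weight loss. Over slope SDs of 3 to 10 kg per 6 months and moderate differential dependence, it runs from a few tenths of a kg to about 3 kg. It can therefore reach or exceed 1.26–1.29 kg, but several plausible cases stay below that. To say that it will reach that size would go beyond the documents.

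**What to change.** In Aim 1, Analysis, add a random patient slope for time from baseline, with intercept-slope covariance, to the primary model. Add a sensitivity analysis using one follow-up weight per index episode: the weight nearest month 6 within the planned window, with its actual time in the model. Inverse-intensity weighting of visits is an alternative. Report the number of follow-up weights per patient by condition, so that readers can judge whether visit patterns differ.

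The random slope is the better primary change because it keeps all the data. The cost is wording only, with no new data collection, slightly more model complexity and usually a wider confidence interval. The single-weight analysis discards some within-patient information. Some bias remains under either approach when visits depend on unobserved trajectory or when patients never return.

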Primary care is undergoing rapid transformation with a shift toward population-based approaches that prioritize preventive care. Initiatives such as pay for performance, the Patient-Centered Medical Home [10], and efforts associated with the Affordable Care Act [11] have brought a host of structures, tools, and processes not previously available, creating new opportunities to engage patients in efficacious programs. Many practices now have electronic medical records (EMRs), patient registries, and a team approach to care that may include expanded care visits with care managers, dietitians, and social workers or psychologists [12, 13]. Increasingly, value-based payment models incentivize practices to identify patients at high risk for complications of chronic conditions and to mitigate these risks. Many of these chronic conditions can be improved or alleviated by reducing excess weight.

Importantly, patient demand is high for weight management in primary care*.* A study by Sherson et al. [14] reported that the majority of patients want to discuss weight loss with their physicians. Specifically, patients value physician direction with their diet, physical activity, and goal setting [15]. In addition, recent years have ushered in numerous and diverse options for weight management that extend significantly beyond lifestyle advice. Medications for weight loss are being more extensively studied and demonstrating improved outcomes [16–19]. Bariatric surgery provides a possible option to address weight and reverse potentially life-threatening conditions such as heart disease and diabetes in both adolescents and adults [20–23]. Intensive behavioral therapy (IBT) for obesity is now a covered benefit under Medicare [24]. Together, primary care practice transformation, reimbursement for obesity care, and better therapies for weight management suggest new and pragmatic approaches can emerge.

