### Data collection and management

De-identified data will be extracted from Epic (the electronic medical record) from March 17, 2020, to March 16, 2021, then every 6 months from March 17, 2021, until September 17, 2025. The study timeline is depicted in a SPIRIT diagram in Fig. 3. Data extraction will be performed by Health Data Compass, the Colorado Center for Personalized Medicine’s cloud-based enterprise data warehouse and management platform. Health Data Compass extracts de-identified data using a proprietary process, wherein all data are checked for process compliance and missingness prior to release to the study team. As these data are de-identified, informed consent was not utilized. However, a written informed consent process was utilized for specified, individually contacted patients and practice members for the purposes of the implementation evaluation.

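### Calendar period adjusts the level of weight, but the primary test is on weight change over patient time, so that coefficient gets little or no adjustment for secular trends

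*Protocol article*

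**What the plan says.** The Aim 1 Analysis section of the Protocol article sets out a mixed model for repeated weights: "The mixed model will include random intercepts for patient, provider, and clinic, along with fixed effects for time and intervention condition". Time enters in two ways. The first is "calendar time, divided into four 1-year periods and included as a categorical variable to flexibly model its effect on the outcome", which the article says is there to deal with temporal trends. The second is continuous patient time, counted from baseline. One interaction is named: "An additional fixed effect for the interaction between patient time and intervention condition will be used to estimate the parameters of primary interest". The test is on that term: "The primary analysis will test the null hypothesis that the interaction effect coefficient is equal to zero". On follow-up, "weight collected from baseline to approximately 9 months post-baseline for the individual patient will be included in the primary analysis".

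The article names no interaction between calendar period and patient time. It also does not say whether a weight's period is that of the patient's index visit or that of the date on which the weight was taken.

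**The concern.** In a stepped wedge, condition is tied to calendar time by design: all clinics begin in standard of care and, after three yearly steps, all are in PATHWEIGH in the fourth year. Randomization of sequence does not remove this; period adjustment has to, and it has to act on the parameter being tested.

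Here that parameter is a slope contrast, and the period terms act on the level. Standard-of-care patients in every year share one slope, and so do PATHWEIGH patients. If 6-month weight change in these clinics moves over the years for reasons unrelated to PATHWEIGH, the movement goes into the patient-time by intervention term.

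The article gives grounds for not assuming stability. The Background states: "Medications for weight loss are being more extensively studied and demonstrating improved outcomes". Data collection opens in the first pandemic year: "De-identified data will be extracted from Epic (the electronic medical record) from March 17, 2020, to March 16, 2021". At stake is the trial's one primary test, which could show a spurious benefit or mask a real one.

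**Working it through.** **1. What the tested coefficient estimates.** Let x be patient time in units of 6 months, X the condition (0 or 1) and p the calendar period. The fixed part as written is

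E(weight) = β0 + γ_p + β1·x + β2·X + β3·x·X.

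With period set by index visit, γ_p is the same at baseline and follow-up and cancels from the change. Expected 6-month change is β1 in control and β1 + β3 in intervention, whatever the year. So β3 is mean change under PATHWEIGH minus mean change under standard of care, with calendar years pooled. With period set by measurement date, γ changes within a patient only when a follow-up weight falls in a later period, so it absorbs part of a trend but not the year-specific slope.

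**2. Calendar gap between conditions.** Inputs: 20, 18 and 19 clinics (Table 1), four 1-year periods, three steps, all clinics starting in control. Equal enrolment per clinic-year is assumed.

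- Control clinic-years: 20×1 + 18×2 + 19×3 = 113. Sum of study years: 20×1 + 18×(1+2) + 19×(1+2+3) = 188. Mean 188/113 = 1.66.
- Intervention clinic-years: 20×3 + 18×2 + 19×1 = 115. Sum: 20×(2+3+4) + 18×(3+4) + 19×4 = 382. Mean 382/115 = 3.32.
- Gap: 3.32 − 1.66 = 1.66 years.

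**3. Bias.** If 6-month change drifts by d kg per year and PATHWEIGH has no effect, β3 tends to 1.66d under index coding. Under measurement-date coding, separate calculations with different assumed visit timings gave about 1.2d to 1.4d, so roughly 15-30% is absorbed. The values of d below are assumptions; the article gives none.

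| d (kg per year, either sign) | Bias, index coding (kg) | Bias, measurement-date coding (kg) |
|---|---|---|
| 0.10 | 0.17 | 0.12-0.14 |
| 0.25 | 0.41 | 0.30-0.35 |
| 0.50 | 0.83 | 0.60-0.70 |
| 1.00 | 1.66 | 1.2-1.4 |

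The smaller detectable difference in the Sample size section is 1.26 kg. Drift alone would produce it at 1.26/1.66 = 0.76 kg per year under index coding.

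A simulation of the written model agreed. It used 57 clinics, 30 patients per clinic-year, 150 runs, no true effect, and assumed patient SD 20 kg, clinic SD 3 kg and residual SD 10.7/√2 kg. Under index coding, improving drifts of 0.10, 0.25, 0.50 and 0.76 kg per year gave mean estimates of −0.18, −0.43, −0.85 and −1.28 kg. With index period by patient time added, the mean estimate was −0.03 kg at every drift, the same as with no drift, so what remains is simulation noise.

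**4. The plan's own power figure.** The Hussey-Hughes variance for a change outcome with categorical period effects is

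Var = Iσ²(σ² + Tτ²) / [(IU − W)σ² + (U² + ITU − TW − IV)τ²],

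with I = 57, T = 4, U = 115, W = 20² + 38² + 57² = 5093, V = 20×9 + 18×4 + 19×1 = 271, σ² = (1 − ICC)/30 and τ² = ICC. Then IU − W = 1462 and U² + ITU − TW − IV = 3626.

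- ICC 0.02: Var = 0.2098/120.28 = 0.001744, SE 0.0418; times 2.80 gives 0.117 (stated 0.118).
- ICC 0.05: Var = 0.4182/227.60 = 0.001837, SE 0.0429; times 2.80 gives 0.120 (stated 0.121).
- Without period effects: about 0.072 at either ICC, which does not match.

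The stated figures therefore fit a period-adjusted contrast of weight change.

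**5. Cost in precision.** In the simulation the standard error rose from 0.217 to 0.323 kg under index coding (ratio 1.49) and from 0.247 to 0.320 kg under measurement-date coding (1.30). From step 4 at ICC 0.02 the ratio is 0.1170/0.0716 = 1.63; at ICC 0.05 it is 0.1201/0.0715 = 1.68.

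**The case against.** The article condenses a fuller plan, states the intent to account for temporal trends, and does put period in the model; an analysis plan that is not shown may hold the missing term. That is a fair limit on certainty. But the article lists the model's terms and singles out one interaction as the additional one, and the model so described does not deliver the stated intent for the coefficient it tests.

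Four stronger readings are tempting and not supported:

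- *The tested effect has no calendar adjustment at all.* That holds only for index-visit coding. Under measurement-date coding there is some adjustment, and the article does not say which applies.
- *A PATHWEIGH benefit would be an artefact of trend.* The article quantifies no drift. The effect of a first year beginning in March 2020 has no stated direction. Aim 2 treats anti-obesity prescribing as a mediator, so part of any rise in prescribing after rollout could be intervention effect. At 0.1 kg per year the bias is small.
- *False-positive rates can be read off the design.* They depend on variance components that the article does not give, so none are claimed here.
- *The power calculation contradicts the analysis.* Powering on a simpler model than the one analysed is common, and only one alternative, no period effects, was compared. The match in step 4 is supporting evidence only.

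**Conclusion.** The point stands in this form: the primary test, as published, has no adjustment or only slight adjustment for secular trends in weight change, depending on how period is coded. The bias is about 1.66 kg per 1 kg-per-year drift under index coding and about 1.2-1.4 kg under measurement-date coding, in either direction.

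The 1.66-year gap rests on the stated design plus equal enrolment per clinic-year. The article itself expects that rollout may increase weight-prioritized visits, which would change the gap. The drift is an assumption throughout. That the slope contrast lacks period adjustment follows from the listed terms and needs no assumption about drift. Because this is the sole primary test and the repair is small, it should be settled before analysis.

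**What to change.** Define calendar period by index-visit date. Add period by patient time to the primary model, or equivalently model 6-month change with period main effects. Test patient time by intervention, and report the 6-month difference, with those terms present. Apply the same rule in the per-protocol analysis and in the analysis of all patients eligible on age and BMI.

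The cost is three coefficients and a standard error about 1.3 to 1.6 times larger (nearer 1.7 at ICC 0.05). Since the stated detectable effects of 0.118 to 0.121 match a period-adjusted contrast of change, the planned power already allows for this.

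The change removes the drift bias only. The model has random intercepts and no random slopes, which is a separate matter: in one simulated setting with a patient slope SD of 10 kg per 6 months, the model standard error after the fix was 0.085 kg against an empirical 0.39 kg. Adding period by patient time does not by itself secure the type I error.
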